### Participant withdrawal

If the participant gives verbal consent for the paramedic to proceed with the blood sample, but loses capacity before the blood is drawn, the participant will be withdrawn from the study. All data and samples collected up to this point will be destroyed as we will be unable to obtain written informed consent. In the event that written informed consent cannot be obtained from the participant for any other reason, the participant will be withdrawn from the study. As above, all data and samples collected up to this point will be destroyed.

In the event that a patient who has given written informed consent loses capacity before the 30-day follow-up, the participant will be withdrawn from the study. Any identifiable data or tissue collected up to this point would be retained and used in the study as written consent had been given. The participant would not be followed up at 30 days.

If at any time, the study team believes that remaining on the study is not in the participant’s best interest, they will approach the participant directly to discuss withdrawal from the study. However, if their withdrawal is recommended from their primary caregiver or a relative due to psychological distress or a similar reason, the study team will not seek to contact the participant any further and they will be withdrawn from the study. Any identifiable data or tissue collected up to this point would be retained and used in the study as consent had been given.

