#### Hospital environment

On arrival at the hospital, all patients will undergo reference standard troponin testing in accordance with contemporary national and international guidance. Acceptable protocols for reference standard troponin testing include:

If a contemporary (not high sensitivity) troponin assay is used: laboratory-based troponin testing on arrival and either 6 hours after arrival, or 10–12 hours after the onset of peak symptoms.If a high sensitivity troponin assay is used: laboratory-based troponin testing on arrival and either 3 hours after arrival, or 6 hours after the onset of peak symptoms, unless the patient has undergone investigation according to a validated rule-out protocol as advocated in national international guidelines.

A high-sensitivity troponin assay is defined as an assay that can detect troponin concentrations in at least 50% of apparently healthy individuals with a co-efficient of variation of <10% at the 99th percentile cut-off.

When the patient arrives at the ED, the local study team will be informed. A member of the study team will either send the lithium heparin sample drawn in the prehospital environment up to the central laboratory for processing and storage, or the sample will be processed and stored by a member of the study team who has had appropriate training. Once the patient has received all initial treatment in accordance with routine care, a member of the local research team will then approach them to answer any questions they may have about the study and obtain written informed consent.

If the research team cannot obtain written informed consent at the time of participant admission to the ED, the research paramedic will follow this up and obtain written informed consent via post, electronically or over the phone. The research paramedic will have 4 weeks to obtain written informed consent before the participant is withdrawn from the study and their samples destroyed. The participant will be made aware of this deadline in the information that is sent to them before they are approached for consent. If the participant is followed up via postal consent, a 1-week grace period will be given to allow for delays in the postal service. After this, the participant will be withdrawn from the study and their study data and samples will be destroyed.

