### Follow-up

Patients will be followed up by reviewing clinical records relating to their inpatient course, including data from serial troponin testing; other laboratory analyses; length of stay; all imaging investigations and procedures and details of any haemorrhagic complications. We will also contact the participant’s primary care practitioner after 60 days to obtain information about any additional relevant events occurring within 30 days of the initial ambulance call. In the small percentage of cases where participants do not have a primary care practitioner, we will contact participants directly after 30 days. If this is not possible and the participant is lost to follow up, then this will be recorded on the electronic case report form.

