### Outcomes

The primary outcome will be a diagnosis of AMI, established at the time of initial hospital admission. To diagnose AMI according to internationally accepted standards requires serial troponin sampling. This will help to ensure adequate reference standards for the diagnosis of AMI. Outcomes will be adjudicated by two independent investigators with reference to relevant clinical information but blinded to the results of research investigations. Discrepancies will be resolved by a third independent investigator. AMI will be defined according to the Fourth Universal Definition.^11^ By virtue of the inclusion criteria, all patients will have symptoms and signs consistent with myocardial ischaemia. Briefly, therefore, patients will be deemed to have met this outcome if they develop a rise and/or fall of troponin to above the 99th percentile.

The secondary outcomes will include any major adverse cardiac events, which include cardiovascular death, coronary revascularisation and incident AMI within 30 days. All causes of death occurring within 30 days and the final diagnoses of all patients will also be recorded.

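### The withdrawal rules stop 30-day follow-up after loss of capacity and destroy data when late consent fails, so losses may depend on the outcome

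*Protocol article*

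**What the plan says.** The protocol article has two separate rules in its Participant withdrawal section.

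- **After written consent.** If any "patient who has given written informed consent loses capacity before the 30-day follow-up, the participant will be withdrawn from the study". The consequence is explicit: "The participant would not be followed up at 30 days". The same paragraph protects what has already been gathered: "Any identifiable data or tissue collected up to this point would be retained and used in the study as written consent had been given".
- **Before written consent.** Apart from loss of capacity before the blood draw, which has its own sentence, the rule is that if "written informed consent cannot be obtained from the participant for any other reason, the participant will be withdrawn from the study". Whatever had been gathered from that person is then destroyed, blood included.

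Three other sections bear on these rules.

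- **Hospital environment.** Written consent is normally sought in the emergency department after initial treatment. If that fails, "The research paramedic will have 4 weeks to obtain written informed consent before the participant is withdrawn from the study and their samples destroyed". Postal consent has one further week.
- **Follow-up.** Inpatient events come from clinical records. The team also contacts the "primary care practitioner after 60 days to obtain information about any additional relevant events occurring within 30 days of the initial ambulance call". Participants are contacted directly only if they have no such practitioner.
- **Outcomes.** The primary outcome is AMI at the initial admission. MACE comprises "cardiovascular death, coronary revascularisation and incident AMI within 30 days". The section also undertakes to record every death within 30 days, whatever the cause, and every patient's final diagnosis.

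**The concern.** The study is meant to support leaving very-low-risk patients at home, so its credibility rests on catching the few bad outcomes in that group. Death is a component of MACE, and loss of capacity can follow a cardiac arrest, shock or another serious complication. A rule that ends observation at loss of capacity, or erases a participant who could not sign, may therefore remove people because of the outcome under study. The sample-size allowance for loss to follow-up and missing data restores numbers; it does not correct selective loss.

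The post-consent loss also looks avoidable, because the follow-up route seldom needs the participant. And the rules sit badly with the undertaking on 30-day deaths: a withdrawn participant who is not followed up cannot have a later death recorded.

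**Working it through.** **1. The rules side by side**

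| Situation | Data already collected | Later events | Outcome affected |
|---|---|---|---|
| Written consent, then loss of capacity before day 30 | Kept | Not collected | Mainly 30-day MACE and death |
| No written consent obtained for any other reason | Destroyed | Not collected | Primary AMI outcome and 30-day MACE |
| Written consent, then death with capacity kept until then | Kept | Collected by the normal route | None; not a withdrawal reason |

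The consent window is 4 × 7 = 28 days, or 35 days by post, against a 30-day outcome window. On the fallback route, most or all of that window can pass before consent is settled.

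Primary care is contacted only after day 60. Someone withdrawn before day 30 would therefore contribute no primary-care information. The text does not say whether events that preceded withdrawal, but had not yet been extracted, count as already collected.

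**2. Direction of the effect of lost events**

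- MACE incidence: removing events lowers it; if no events are lost, this effect is absent.
- NPV = true negatives / (true negatives + false negatives). Removing a false negative raises it; removing a true positive leaves it unchanged.
- Sensitivity = true positives / all events. The sign depends on whether T-MACS detects lost events more or less often than retained ones. Suppose 10% of events are lost and sensitivity among the retained is 95%. If the lost ones would be detected 80% of the time, true sensitivity is 0.9 × 95% + 0.1 × 80% = 93.5%, so the observed value is 1.5 points too high. If they would all be detected, it is 0.9 × 95% + 0.1 × 100% = 95.5%, so the observed value is 0.5 points too low.

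**3. Inputs for an illustration**

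The Sample size section gives 605 analysed participants, 10% prevalence, 45% specificity, and an assumed sensitivity and NPV of 100%.

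- Events: 605 × 0.10 = 60.5, taken as 60.
- True negatives: (605 − 60) × 0.45 = 245.25, taken as 245.

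These inputs are for index AMI. The article gives no 30-day MACE rate and no expected number of withdrawals.

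**4. The plan's own figures**

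With no false negatives, the exact two-sided 95% lower limit is 0.025^(1/n).

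- Sensitivity: 0.025^(1/60) = 94.0%, which agrees with the stated bound of more than 90%.
- NPV: 0.025^(1/245) = 98.5%, which does not reach the stated bound of more than 99%. That is a separate matter and is not used here beyond serving as the starting value.

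**5. Adding back lost events** (Clopper-Pearson lower limits)

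| Lost events restored | Sensitivity | Lower limit | NPV | Lower limit |
|---|---|---|---|---|
| None | 60/60 = 100% | 94.0% | 245/245 = 100% | 98.5% |
| 1 or 2, all T-MACS positive | 61/61 or 62/62 = 100% | 94.1% or 94.2% | 245/245 = 100% | 98.5% |
| 1, very low risk | 60/61 = 98.4% | 91.2% | 245/246 = 99.6% | 97.8% |
| 2, very low risk | 60/62 = 96.8% | 88.8% | 245/247 = 99.2% | 97.1% |

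If MACE numbered 90 instead, true negatives would be (605 − 90) × 0.45, about 232. Two lost very-low-risk events would then move the sensitivity lower limit from 96.0% to 92.4%, and the NPV lower limit from 98.4% to 96.9%.

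**The case against.** The strongest reply is that the reach is narrow. Data up to loss of capacity are retained, so an arrest or index AMI already documented before withdrawal stays in. Consent in the emergency department is the normal route; the 4-to-5-week route is the fallback. Death after consent in someone who kept capacity is not a withdrawal reason and is captured by records and primary care. People may also lose capacity for reasons unrelated to the heart. The consent design has ethics approval and drew on patient representatives. Recruitment began in February 2019, so revised wording may not cover forms already signed.

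All of this stands, and it limits what may be claimed. A reader might infer that MACE is observed only in people who stayed well, or that every accuracy measure is biased upward. The documents do not support either: retention and the normal consent route preserve many serious events, and sensitivity can move in either direction. Nor does the article name death before consent. That it falls under the any-other-reason rule is a plain reading of the text, not a statement in it.

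A worst-case analysis or an exclusion tally may well be specified in a fuller document, so their absence from the article is not the point. The point is an explicit rule that ends obtainable follow-up and conflicts with another section. Ethics approval explains such a rule but does not remove its effect.

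**Conclusion.** The point holds, and the rule should be changed. The post-consent rule creates an avoidable and possibly outcome-dependent loss of 30-day events, and it contradicts the undertaking to record all deaths within 30 days. The pre-consent rule can remove participants entirely and so can also touch the primary AMI outcome; it may be harder to change.

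The size cannot be determined from the article. The range starts at no effect on NPV and essentially none on sensitivity, when every lost event was T-MACS positive. At the other end of the illustration, two lost very-low-risk events would take the sensitivity lower limit to 88.8%, below the 90% that the protocol set as its benchmark for the primary outcome. This rests on event counts borrowed from the AMI sample size, on no observed false negatives, and on an assumed number of lost very-low-risk events. Nothing in the article shows that any such event would be lost. The case for change is that a few would matter and that most of the post-consent loss could be prevented.

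**What to change.** - **Reconcile** the Participant withdrawal, Follow-up and Outcomes sections. For participants who gave written consent and then lose capacity, continue the 30-day follow-up from records and primary care under that consent, with an amendment to the consent wording where required.
- **Where this is not permitted**, use events recorded up to withdrawal and add a worst-case sensitivity analysis of 30-day accuracy that counts the unobserved remainder as events. State in the Outcomes section that deaths among these participants may be unknown.
- **For people without written consent**, keep a non-identifiable tally by reason (death, lost capacity, refusal, no reply) and report it beside both the primary and the 30-day results.

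The cost is approval time, new consent wording and one extra analysis. The wording may not cover participants already enrolled, and the results may look slightly less favourable.

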### Outcomes

The primary outcome will be a diagnosis of AMI, established at the time of initial hospital admission. To diagnose AMI according to internationally accepted standards requires serial troponin sampling. This will help to ensure adequate reference standards for the diagnosis of AMI. Outcomes will be adjudicated by two independent investigators with reference to relevant clinical information but blinded to the results of research investigations. Discrepancies will be resolved by a third independent investigator. AMI will be defined according to the Fourth Universal Definition.^11^ By virtue of the inclusion criteria, all patients will have symptoms and signs consistent with myocardial ischaemia. Briefly, therefore, patients will be deemed to have met this outcome if they develop a rise and/or fall of troponin to above the 99th percentile.

The secondary outcomes will include any major adverse cardiac events, which include cardiovascular death, coronary revascularisation and incident AMI within 30 days. All causes of death occurring within 30 days and the final diagnoses of all patients will also be recorded.

### Statistical analysis

#### Primary analysis

We will determine the output of the T-MACS decision aid using the original, predetermined algorithm. This algorithm computes the probability that each patient has a diagnosis of ACS and stratifies patients into four groups on the basis of that probability, as follows: very low risk (<2% probability)—ACS can be considered ruled out. We hope our findings will justify avoiding transport to hospital in this group; low risk (2%–5% probability): this group requires serial troponin sampling, which could be taken in an ambulatory care setting; moderate risk (5%–95% probability): this group requires serial troponin sampling but may also require additional imaging and therefore requires transfer to hospital; high risk (≥95% probability): ACS is ‘ruled in’ for this group, which could facilitate direct transfer to a specialist centre, facilitating early coronary intervention.

We will calculate the diagnostic accuracy of T-MACS as a ‘rule-out’ tool by dichotomising the probability at a threshold of 2%. We will then calculate sensitivity, specificity, positive and negative predictive values, positive and negative likelihood ratios and their respective 95% CIs. We will also report the number and percentage of patients with ACS stratified by T-MACS risk group. The proportion of transfers to the ED that could have been avoided will be calculated.

#### Secondary analyses

We are planning to conduct several secondary analyses. First, we will evaluate the diagnostic accuracy of T-MACS as a ‘rule-in’ tool, which would facilitate direct transfer to tertiary care heart attack centres and may enable patients to benefit from earlier specialist treatment such as percutaneous coronary intervention in future. To do this, we will dichotomise T-MACS at the probability threshold of 95% (ie, analysing classification as ‘high risk’ vs all other risk groups). We will again calculate sensitivity, specificity, positive and negative predictive values, positive and negative likelihood ratios and their respective 95% CIs. Finally, we will calculate the proportion of patients with and without ACS who would have been transported to tertiary care facilities if T-MACS had been used in practice, and we will compare those findings to the observed practice in routine care. As some patients may have final diagnoses other than ACS, we will also retrieve the final coded diagnosis for all patients and present a descriptive analysis stratified by T-MACS risk group.

Second, we will evaluate the diagnostic accuracy of other hospital-based strategies used to rule-out, rule-in or ‘risk-stratify’ patients with AMI or ACS such as the HEART (History, ECG, Age, Risk factors, Troponin) score, History and ECG only Manchester Acute Coronary Syndromes (HE-MACS) decision aid, limit of detection strategy and selected cut-offs (eg, the 99th percentile of a reference population).

#### Economic analyses

Total direct healthcare costs (resource use × unit costs data) will be calculated using a microcosting study run by our team (ISRCTN 86818215) and will compare the novel diagnostic pathway versus estimates for current care.^12^ Where appropriate, we will proceed to formal cost-effectiveness analysis using a de novo decision-analytic model populated with data collected during this study and other externally published data. The model would extrapolate the effects of implementing the novel diagnostic pathway derived in this work on healthcare resource use and health status (quality adjusted life years as informed by the EQ-5D) versus current diagnostic and treatment pathways. Economic analyses will be led by AT.

### Patient and public involvement

To maximise the potential for clinical impact, this study has been designed in collaboration/consultation with a rounded group of stakeholders including patient and public representatives (eg, the Withington Heart Help Group and the Ticker Club) and industry (we have consulted with numerous manufacturers to confirm that work in this area is currently a high priority). Manchester University NHS Foundation Trust sponsors the study. Our consent procedure has been informed by prior experience within our national network of ambulance services, initial feedback from patient and public representatives (who have agreed with concern that judgement may be clouded in this acute situation) and the experience of AS in the Wellcome-funded ‘Network Exploring Ethics in Ambulance Trials (NEAT)’ project.^13^

## Dissemination

Following completion of our analysis, we will discuss the significance of our findings and the key messages to be communicated at meetings of the Trial Steering Committee, Trial Management Group and Patient Advisory Group. Following this, we will finalise our dissemination strategy. We will aim to publish our findings (positive or negative) in a high impact general medical journal with a relevant target audience (eg, British Medical Journal; The Lancet). In addition, we aim to present our findings to relevant target audiences at national and international conferences (eg, Royal College of Emergency Medicine Annual Scientific Conference; European Society of Cardiology Annual Conference).

If our findings are positive, we will also develop an implementation strategy. This will involve working with commissioning groups (including NHS England and the Greater Manchester Joint Commissioning Board), NICE and Ambulance NHS Trusts to make the case for the clinical and cost effectiveness of our technology. Template clinical guidelines and training guides will be disseminated to ambulance services, and we anticipate proceeding to support pilot evaluations with a view to larger scale clinical implementation within 2 years.

Finally, we will work with stakeholder organisations including the National Ambulance Research Steering Group (NARSG; AS is a member) and the International Federation of Clinical Chemistry Committee for Cardiac Biomarkers (RB is a member) to enhance communication of our findings within the field.

## Discussion

Based on our experience with previous studies, if our findings are positive we will aim to achieve clinical implementation within 2 years. Clearly, this will involve additional work to demonstrate the feasibility and acceptability of ‘live application’ of T-MACS in the ambulance; to develop new clinical guidelines and training regimes and to robustly communicate the clinical and cost effectiveness of the strategy.

The recent update to NICE Guideline CG95 incorporated a novel diagnostic strategy (originally developed by our group) for in-hospital use based on data from observational studies with a similar design. Given that precedent, we anticipate that our findings will generate the evidence required by NICE to issue a recommendation for the clinical use of T-MACS with a POC troponin assay in the prehospital environment.

We also implemented T-MACS in the hospital environment primarily based on observational data. The algorithm has been applied in 8000 patients and has led to 2/3 patients being safely treated in an ambulatory care environment without requiring hospital admission. Health Innovation Manchester, with access to a Joint Commissioning Board, has adopted T-MACS as an exemplar project for rapid implementation across Greater Manchester. We will conduct a ‘phase 4 evaluation’ of that regional implementation, aiming to achieve more widespread clinical implementation within 24 months of completion. If the findings of the proposed study are positive, we will use a similar methodology to achieve rapid implementation in the prehospital environment.

If successfully implemented in practice, we anticipate that our findings will avoid the need for unnecessary ambulance transfers and hospital admission in approximately 40% of patients. As chest pain is the second most common reason for emergency ambulance calls and most common reason for emergency hospital admission, this is likely to have a substantial economic impact while reducing hospital overcrowding and its associated complications.
